### Treatment as usual

The control condition in this trial is a TAU control group for comparison with the intervention group. TAU in this trial does not refer to a specific treatment regimen but rather to unconstrained services that may vary across participants. Participants randomized to the TAU group will be informed that they should continue receiving their usual care from their GP, specialist physician or other health professional(s) according to their needs. Control participants will be requested not to engage in any mindfulness program until the trial has been completed; nevertheless, as part of the post-intervention questionnaire, control participants will be asked whether they have initiated a mindfulness program themselves, providing an opportunity to control for confounding in the subsequent analyses should some have in fact done so. The treatments that the participants will receive will be registered for both the intervention group and control group as part of the trial.

### Measurements

All outcomes will be measured at baseline, post-treatment, and at the follow-ups at 6 and 12 months.

#### Primary outcome

##### The Quick Environmental Exposure and Sensitivity Inventory

The Quick Environmental Exposure and Sensitivity Inventory (QEESI) has been developed as a screening instrument for MCS designed to facilitate history-taking from individuals who report chemical intolerance [42]. It consists of five scales, of which this study will use the three: symptom severity, chemical intolerances, and life impact, each containing 10 items and producing a score ranging between 0 and 100. The Life Impact Scale (LIS) of the QEESI, which is the primary outcome measure, asks the participant to consider how much their reactions have affected various aspects of their life in terms of parameters such as diet, ability to go to work or school, ability to be around others and enjoy social activities, and relationship with spouse and family.

A Danish translation of the QEESI has been evaluated in terms of internal consistency, test-retest reliability, sensitivity, and specificity, and in order to establish normative data [43]. The psychometric properties of QEESI were found to be satisfactory, which is in accordance with other similar studies [42,44].

#### Secondary outcomes

##### Symptom-Check List-92

The Symptom Checklist (SCL-92) is a self-administered questionnaire for measuring psychological distress or the degree of affective distress. The questionnaire covers nine dimensions; however, only the somatization, depression, and anxiety scales will be used in this study. The items are measured on a five-point Likert scale. The SCL-92 has been translated into Danish, and has been psychometrically evaluated in a Danish population, showing that the non-psychotic scales function well and seem to reflect a single broad dimension of stress [45].

##### World Health Organization Quality Of Life, Brief Version

The World Health Organization Quality of Life (WHOQOL-BREF) is a relatively short multidimensional questionnaire, which is a generic measure of health-related quality of life. The questionnaire comprises the domains of physical health, psychological wellbeing, and social conditions and environment, as well as a general QOL domain. The questionnaire has been shown to have good psychometric properties and to adequately assess domains relevant to QOL in a large number of cultures worldwide [46].

##### Perceived Stress Scale

The Perceived Stress Scale (PSS) is designed to measure the degree to which situations in a person’s life are appraised as stressful [47]. The PSS was designed for use with community samples with at least a secondary school education. The items are easy to understand and the response options are simple to grasp [48]. The PSS has been adapted to a short version consisting of 10 questions, the PSS-10, which has proven to be a valid and reliable measure of perceived stress [48].

##### Brief Illness Perception Questionnaire

The Brief Illness Perception Questionnaire (Brief IPQ) has nine items and is designed to measure patients’ cognitive and emotional representations of their illness. Five items assess cognitive illness representations, two items assess emotional representations, and one item assesses illness comprehensibility. The items are rated using a response scale of 0 to 10. Each causal item is grouped into categories (for example, stress, lifestyle, hereditary factors), which are determined by the particular item studied. The Brief IPQ has been found to have good test-retest reliability and validity [49].

##### Role Work Functioning Index

The Role Work Functioning Index (RWFI) is a measure of work ability, a concept that refers to the balance between the demands of a job and the individual’s capacity to master these demands. As opposed to most instruments that assess work ability, the RWFI does not ask respondents to consider their health when responding to questions about their work ability. The index consists of seven questions tapping into the following dimensions of work demands: tempo; workload; and physical, social, and cognitive job demands ([name], 2011, personal communication).

### Mediators

#### Rumination-reflection questionnaire

The rumination subscale of the Rumination-Reflection Questionnaire is a 12-item questionnaire measuring the tendency to recurrently think about threats, losses, or injustices to the self [50]. The scale has been found to tap into a type of self-attentiveness closely linked to the personality trait of neuroticism. The authors reported an internal consistency coefficient of 0.90 for the rumination subscale.

#### Self-Compassion Scale

The Self-Compassion Scale measures the ability to have a healthy stand towards oneself that does not involve evaluations of self-worth [51]. Research has shown that self-compassion is associated with wellbeing and greater psychological health. The questionnaire used in this trial is a short form consisting of 12 questions, which has been shown to have a high level of correlation with the original questionnaire [52].

#### Five Facet Mindfulness Questionnaire

The Five Facet Mindfulness Questionnaire (FFMQ) assesses five general facets of being mindful in daily life: observing, describing, acting with awareness, non-reactivity to inner experience, and non-judging of inner experience. Items are rated on a five-point Likert scale ranging from 1 (never or very rarely true) to 5 (very often or always true). Previous studies have provided good support for construct validity of the FFMQ; furthermore, four of the five facets (except for ‘acting with awareness’) have been found to be significantly correlated with meditation experience [53].

### Statistical analysis

Statistical analyses will be conducted using the latest version of SPSS. Group allocation (intervention or control) will be concealed for the statistician who will perform the statistical analyses. Descriptive statistics for the two groups will be generated. In the statistical analyses of a possible effect, the mixed model repeated measures method will be used to test the effect of the intervention and the effect of time. Level of significance will be set at *P* < 0.05. All effect measures will be inspected for normality, and transformed as appropriate. Missing values will be handled by the multiple imputation method. Data analysis will be performed based on the intention-to-treat principle, meaning that all participants will be included in the analysis irrespective of their compliance with the intervention protocol. Lastly, an additional per-protocol analysis will also be conducted.

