### Randomization

The randomization will be carried out as follows. Once we have recruited 16 to 20 eligible participants (the number of participants required to start off a MBCT group) who have signed a written consent form, they will be randomized by a computer-generated allocation sequence either to intervention with MBCT or to the TAU control condition. The randomization will be pre-programmed so as to produce equal numbers in both groups. The randomization procedure will be carried out at the Research Centre for Chemical Sensitivities by a researcher who is otherwise not involved in the trial, thus securing concealment to the research team. Once the randomization has been carried out, the first author will contact participants by telephone and email to inform them about the allocation.

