### Intervention

The mindfulness-based intervention in this RCT is modeled on MBCT, which is a group skills-based training approach developed to prevent relapse of depressive episodes [39]. MBCT is partly based on the mindfulness-based stress reduction (MBSR) program developed by Kabat-Zinn [40], and partly on cognitive therapy for depression. MBCT focuses on the aspect of ‘de-centering’, meaning not accepting the content of thoughts as facts and not identifying with thoughts [39]. The MBCT program has been fully manualised by Segal and colleagues, describing the exercises and rationale in detail [41]. However, as the original program was developed to prevent relapse of depression, some minor modifications will be made to the curriculum in this trial to adapt it for individuals with MCS. For example, session seven in the MBCT program deals with identifying signs of depressive relapse, but in our study, the emphasis will be on applying mindfulness in coping with stress. The main treatment component will be mindfulness exercises, which includes various forms of meditation and yoga. The purpose of the mindfulness exercises is to cultivate the ability to stay in the present with full awareness, and to practice an attitude of acceptance of whatever sensation, pleasant or unpleasant, that arises in the present moment. Before commencing the program, all the participants will be invited to an individual session with the group therapist with the aim of getting to know the participants and answering questions about the program. The program will be given to groups with a maximum of 15 participants, and will comprise eight weekly sessions, each 2.5 hours long, plus a half-day of silent retreat between weeks 6 and 8. Additionally, during the program, participants will be encouraged to do home work assignments of up to 45 minutes 6 days a week. Guided instructions will be provided on a CD for home practice. If a participant is unable to attend a session, they will be e-mailed any written material handed out during the class. Finally, participants will be offered follow-up sessions at months 1, 3, and 6 post-treatment.

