The therapists teaching mindfulness in the trial will be two clinical psychologists, both of whom have extensive experience in delivering mindfulness-based treatment. They have undergone formal education in mindfulness-based therapies from The Oxford Mindfulness Centre and from the Umass Centre for Mindfulness in Medicine, Healthcare, and Society, respectively.

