### Sample size

The sample size estimation is based on the primary effect measure, the QEESI. Results from a recently conducted study evaluating a Danish translation of the QEESI, showed that the patient sample had a mean value of 61.5 with a standard deviation of 24.3 on the LIS [43]. In this study, a clinical effect will be set as a 25% reduction on the LIS of the QEESI, which we regard as a clinically meaningful reduction in the effect of MCS on participants’ daily lives. With a reduction of 25% on the LIS, the study will need to include 41 experimental subjects and 41 control subjects to be able to reject the null hypothesis, that is, that the population means of the experimental and control groups are equal with probability (power) of 0.8. The type I error probability associated with this test of this null hypothesis is 0.05.

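### MBCT is taught in about four or five classes, but the stated model names no class effect and the sample size assumes independent participants

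*Protocol article*

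**What the plan says.** All places are in the protocol article.

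- **Randomization:** "Once we have recruited 16 to 20 eligible participants (the number of participants required to start off a MBCT group" they are allocated by computer in equal numbers to the two arms. A batch of 16 to 20 therefore supplies one MBCT class of 8 to 10.
- **Intervention:** "The program will be given to groups with a maximum of 15 participants". Fifteen is a ceiling that equal allocation of such a batch does not reach. Also: "The therapists teaching mindfulness in the trial will be two clinical psychologists".
- **Treatment as usual:** control participants continue with whatever individual care they need. They form no groups.
- **Statistical analysis:** "the mixed model repeated measures method will be used to test the effect of the intervention", together with the effect of time. No class, therapist or batch effect is named.
- **Sample size:** "the patient sample had a mean value of 61.5 with a standard deviation of 24.3 on the LIS", and "a clinical effect will be set as a 25% reduction on the LIS of the QEESI". This leads to 41 per arm. No ICC or design effect is mentioned.

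**The concern.** The trial is partially nested: one arm is clustered by the way the treatment is given and the other is not. Classmates share a teacher, eight sessions, a half-day retreat and each other's company, so their Life Impact Scale (LIS) scores may be correlated. The repeated-measures part of a mixed model handles correlation between visits of one person. It does not absorb correlation between people in the same class.

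If that correlation is positive and left out, the confidence interval for the primary effect is too narrow and the test rejects too often. The sample size, built without it, then delivers less than the stated power once the standard error is right.

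**Working it through.** **Inputs from the article.** Mean LIS 61.5, SD 24.3, reduction 25%, power 0.8, type I error 0.05, 41 per arm, batches of 16 to 20 split equally.

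**Assumptions.** Class ICC 0 to 0.10; batch variance 0%, 5% or 10% of the total. The article gives neither.

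**1. The plan's own figure.** Difference = 0.25 × 61.5 = 15.375 points, or 15.375 / 24.3 = 0.633 SD. Normal formula: 2 × [24.3 × (1.960 + 0.842) / 15.375]² = 39.2, so 40 per arm. The two-sided t-test version gives 40.2, so 41. This matches the plan, with nothing left over for clustering. Power at 41 per arm is 0.808 (t-test) or 0.817 (normal).

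**2. Classes.** 41 / 10 = 4.1 and 41 / 8 = 5.1, so about four or five classes.

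**3. Effect of ignoring class.** Only the MBCT arm is clustered, so its design effect 1 + (m − 1) × ICC is averaged with 1 for TAU. The variance of the difference is inflated by

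VI = 1 + (m − 1) × ICC / 2.

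- Type I error without a class term = 2 × [1 − Φ(1.96 / √VI)].
- Power with the correct standard error = Φ(15.375 / [24.3 × √(2 × VI / 41)] − 1.96).
- N per arm to restore power = 41 × VI, rounded up.

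Example, m = 8 and ICC 0.05: VI = 1 + 7 × 0.05 / 2 = 1.175; √VI = 1.084; 1.96 / 1.084 = 1.808; type I error 0.0706.

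| ICC | VI (m = 8; 10) | Type I error | Power, correct SE | N per arm |
|---|---|---|---|---|
| 0 | 1; 1 | 0.0500 | 0.817 | 41 |
| 0.01 | 1.035; 1.045 | 0.0540; 0.0552 | 0.804; 0.800 | 43; 43 |
| 0.02 | 1.070; 1.090 | 0.0581; 0.0605 | 0.791; 0.783 | 44; 45 |
| 0.05 | 1.175; 1.225 | 0.0706; 0.0766 | 0.753; 0.735 | 49; 51 |
| 0.10 | 1.350; 1.450 | 0.0916; 0.1036 | 0.693; 0.662 | 56; 60 |

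**4. Effect of a shared batch.** Both arms of a batch are recruited together, so a batch effect cancels in the comparison. Ignoring it makes the standard error too large. Simulated type I error of a t-test with neither class nor batch (200,000 runs per setting; five classes of 8, 8, 8, 8, 9; four classes of 10, 10, 10, 11):

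| Class ICC | No batch variance (5; 4 classes) | Batch 5% | Batch 10% |
|---|---|---|---|
| 0 | 5.0%; 5.0% | 4.6%; 4.6% | 4.2%; 4.2% |
| 0.01 | 5.4%; 5.5% | 5.0%; 5.2% | 4.5%; 4.7% |
| 0.02 | 5.9%; 6.0% | 5.3%; 5.7% | 4.9%; 5.2% |
| 0.05 | 7.1%; 7.7% | 6.6%; 7.3% | 6.3%; 6.9% |
| 0.10 | 9.4%; 10.6% | 8.9%; 10.2% | 8.4%; 10.0% |

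**5. Degrees of freedom.** Two simple stand-ins for the clustered model show the cost (simulated, 80,000 runs, no batch variance).

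- MBCT class means against individual TAU values, with Satterthwaite degrees of freedom: power 0.75 (five classes) or 0.73 (four) at ICC 0, 0.67 or 0.62 at ICC 0.05, and 0.60 or 0.54 at ICC 0.10.
- Paired differences of arm means by batch, the most cautious treatment of batch: 0.58 or 0.50 at ICC 0, and 0.46 or 0.38 at ICC 0.10.

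The first stand-in ignores batch. With 5% batch variance and class ICC 0 its type I error is only 3.5%, which is why a class term alone is not enough.

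**The case against.** A reader might infer that the plan treats participants as independent. The Statistical analysis section does not say so. It gives no random effects or covariance structure, a mixed model can carry a class effect, and the article condenses a fuller plan that is not shown. That objection stands for the model: the article names no class effect, and no more can be said. It does not reach the sample size, which the article fixes and which reproduces only under independence.

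A reader might also infer that the type I error certainly exceeds 5%. That depends on an ICC that the article does not give. At ICC 0 the error is 5.0%. At 0.01 to 0.02 a shared batch effect can cancel the excess. At 0.05 and above the excess shrinks but remains under every batch variance tried.

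The figures are for a two-group comparison at one time point. The planned model uses baseline and three later assessments, and how a class ICC carries into it was not worked out. The direction stays the same, but the size may differ. Nor is there a calculation to support a claim that a single class would decide the result; one class of five is about a fifth of one arm.

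**Conclusion.** The concern holds in conditional form. The trial is partially nested, the article's primary model names no class effect, and 41 per arm contains no allowance for clustering. If the class ICC is above zero and no class term is fitted, the standard error omits a real source of variation. Over an assumed ICC of 0.01 to 0.10 with classes of 8 to 10, and no batch effect, the type I error is about 5.4% to 10%.

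The stated 80% power holds only without class clustering. With the correct standard error it lies between 0.80 and 0.66 over that range, and lower once the small number of classes is counted. These figures rest on the assumed ICC, on one class per batch, and on a comparison at a single time point.

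**What to change.** 1. Record the MBCT class and the randomisation batch for every participant. Recruitment is still under way, so this is feasible.
2. Add to the primary mixed model a random class effect in the MBCT arm only, with small-sample degrees of freedom (for example Satterthwaite), and adjust for randomisation batch in both arms.
3. Report the class ICC with its interval.
4. In the Sample size section, say that 80% power assumes no class clustering, and give the power over a stated ICC range.

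**Cost.** Two data fields and a few sentences. The interval will be wider, the ICC will be imprecise, and with four or five classes the loss of degrees of freedom is noticeable: in the class-mean approximation power drops to about 0.73 to 0.75 even when the ICC is zero. A class code that exists in only one arm also shows which arm is which to a statistician who is meant not to know the allocation, so the model should be fixed in writing before that field is released.

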### Sample size

The sample size estimation is based on the primary effect measure, the QEESI. Results from a recently conducted study evaluating a Danish translation of the QEESI, showed that the patient sample had a mean value of 61.5 with a standard deviation of 24.3 on the LIS [43]. In this study, a clinical effect will be set as a 25% reduction on the LIS of the QEESI, which we regard as a clinically meaningful reduction in the effect of MCS on participants’ daily lives. With a reduction of 25% on the LIS, the study will need to include 41 experimental subjects and 41 control subjects to be able to reject the null hypothesis, that is, that the population means of the experimental and control groups are equal with probability (power) of 0.8. The type I error probability associated with this test of this null hypothesis is 0.05.

### Ethical considerations

The trial has obtained approval from the regional ethics committee (registration number H-2010-122), and is registered with the Danish Data Protection Agency.

There is no documentation of any side effects or serious risks related to participation in an MBCT program. However, participants may experience unpleasant thoughts and emotional reactions during the program, which we expect to deal with during the group sessions. If this is insufficient, the study therapists will be available for individual counseling, or they may refer participants to relevant treatment elsewhere if considered appropriate. Any adverse events reported by the participants will be registered and reported in future publications.

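### Adverse events are recorded on participant report with no common elicitation stated, while contact with staff differs by arm, so published counts would be open to ascertainment bias if read between arms

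*Protocol article*

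**What the plan says.** Ethical considerations in the protocol article holds the only text on collecting harms: "Any adverse events reported by the participants will be registered and reported in future publications". It gives no question, schedule or collector, and does not say whether the two arms are handled alike. The text just before it concerns the intervention: "participants may experience unpleasant thoughts and emotional reactions during the program, which we expect to deal with during the group sessions". If that is not enough, "the study therapists will be available for individual counseling".

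The section Intervention sets out the contact in the MBCT arm:
- before the start, "all the participants will be invited to an individual session with the group therapist";
- the program itself "will comprise eight weekly sessions, each 2.5 hours long, plus a half-day of silent retreat between weeks 6 and 8";
- afterwards, "participants will be offered follow-up sessions at months 1, 3, and 6 post-treatment".

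Under Treatment as usual, control participants are told that they "should continue receiving their usual care from their GP, specialist physician or other health professional(s) according to their needs". No scheduled session with trial staff is described for them.

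Some channels are common to both arms: the telephone and email contact about allocation (Randomization), the questionnaires at baseline, post-treatment, 6 and 12 months (Measurements), and the registration of treatments received (Treatment as usual, Discussion).

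**The concern.** Recording on participant report works evenly only if both arms have similar occasions to report. Here one arm meets a therapist week after week, in sessions where distress is expected to come up and be dealt with. The other arm is referred back to its own health care. Participants and therapists are also unblinded (Discussion), so what is mentioned or noted as an event can depend on the arm. Blinding the statistician does not help, because the difference arises when the event is recorded.

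At stake is whether the promised harms report can be interpreted. The article says that no side effects of MBCT have been documented and describes this as the first randomized trial of a mindfulness-based intervention for MCS. Readers of a two-arm trial will set the two counts side by side even if no test is planned. If nobody was asked in the same way, no later analysis can repair that.

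**Working it through.** **The plan's own figures.** The article states no adverse event rate and no safety sample size, so there is no safety figure to reproduce. The only figure used here is the arm size of 41 (Sample size), and it reproduces. The difference is 0.25 × 61.5 = 15.375 points with SD 24.3. At two-sided alpha 0.05 (sidedness is assumed) and power 0.80, the normal approximation gives 40 per arm and the t-test gives 40.2, rounded up to 41. Power at 41 per arm is 0.808 by the t-test. The figure serves below only as a denominator.

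**Contacts that could carry a report.**

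| Contact | MBCT | TAU | Section |
|---|---|---|---|
| Individual session before the program | 1 (invited) | 0 | Intervention |
| Weekly sessions | 8 | 0 | Intervention |
| Half-day retreat | 1 | 0 | Intervention |
| Follow-up sessions | 3 (offered) | 0 | Intervention |
| **Therapist contacts, maximum** | **13** | **0** | |
| Allocation contact | 1 | 1 | Randomization |
| Questionnaires after randomization | 3 | 3 | Measurements |

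The sum is 1 + 8 + 1 + 3 = 13. This is a maximum. The individual session comes before the program, so at most 8 + 1 + 3 = 12 contacts can bring out reactions to it, and 3 of those are optional. Individual counseling by the therapists comes on top and is not counted.

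**What unequal capture would do.** Let p be the true risk, equal in both arms, and let c be the probability that an event is recorded. The observed risk is p × c, so the observed risk ratio is (p × c_MBCT) / (p × c_TAU) = c_MBCT / c_TAU, whatever p is. The expected number recorded per arm is 41 × p × c. All values of p and c are assumptions; none comes from the document.

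| c_MBCT | c_TAU | Observed ratio | Recorded events, p = 10% | p = 20% | p = 30% |
|---|---|---|---|---|---|
| 0.9 | 0.9 | 0.9/0.9 = 1.0 | 3.7 v 3.7 | 7.4 v 7.4 | 11.1 v 11.1 |
| 0.9 | 0.6 | 0.9/0.6 = 1.5 | 3.7 v 2.5 | 7.4 v 4.9 | 11.1 v 7.4 |
| 0.9 | 0.3 | 0.9/0.3 = 3.0 | 3.7 v 1.2 | 7.4 v 2.5 | 11.1 v 3.7 |

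For example, 41 × 0.20 × 0.9 = 7.4 against 41 × 0.20 × 0.3 = 2.5. The first row shows that there is no distortion if capture is equal, which is what a shared question aims at.

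**The case against.** The strongest reply is that this is a journal article. The adverse event form and its schedule commonly sit in the full protocol, and the sentence does not say that reports must be spontaneous. In a trial whose outcomes are all questionnaires, a report by a participant could well be a questionnaire answer. This stands, and it makes the point conditional: if the full protocol asks both arms the same question, nothing needs to change. It does not remove the point, because the rule that is stated rests on participant report and the contact described is unequal.

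A reader might also infer more than the text supports:

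- *That a planned safety comparison is biased.* No safety endpoint, hypothesis or between-arm harms analysis appears under Objectives, Hypotheses, Statistical analysis or Ethical considerations. Only registration and reporting are promised.
- *That events under TAU have no route into the record.* They have the allocation contact, the shared questionnaires and the registration of treatments. The post-intervention questionnaire already puts a trial-specific question to controls, about starting mindfulness on their own.
- *That participants who leave the sessions in distress are lost to reporting.* Nothing ties the questionnaires to attendance, and the intention-to-treat rule keeps everyone in the analysis whatever their compliance.

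It is also fair to say that worsening is already partly measured alike in both arms, through the SCL-92 scales, QEESI symptom severity, perceived stress and quality of life, and that care-seeking is registered. What remains uncovered is an explicit question on unwanted effects.

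**Conclusion.** The point holds as a limit on interpretation. As described, harms are recorded when participants report them, with up to 13 therapist contacts in one arm, none scheduled in the other, and no stated elicitation common to both. Counts by arm would be open to ascertainment bias if compared. The likelier direction is towards more recorded events under MBCT, but this is a judgment from the contact pattern and not a result.

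The size cannot be derived. The ratios of 1.0 to 3.0 rest on equal true risk, 90% capture in MBCT and 90% to 30% capture in TAU, all assumed. They show sensitivity to capture and do not estimate it; no single scenario within the range should be quoted as the expected bias. The primary outcome, its test and the sample size are untouched. The improvement is cheap and worth making, and it does not put the trial's main conclusion in doubt.

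**What to change.** Add the same short closed question on unwanted effects to the post-treatment, 6- and 12-month questionnaires in both arms, sent to every randomized participant regardless of session attendance. State in the protocol that any between-arm harms summary rests on those answers, together with the worsening scores and care use already collected in both arms. List events noted in sessions or counseling separately, labelled as coming from a source that only the MBCT arm has.

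The cost is a few items in questionnaires that are already sent, a small added burden on respondents and a minor amendment. Recruitment was ongoing when the article was written (Trial status), so participants who have already passed a time point will lack the answers. The harms summary should therefore give the number asked at each time point. Introducing the question on the same date in both arms of each randomized batch keeps those asked comparable, since each batch of 16 to 20 is split equally between the arms. If the full protocol already contains such a question for both arms, saying so is enough.
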